## Abstract

**Background:**

HIV disproportionately affects Black/African American cisgender women (hereafter women) in the United States. Despite its proven effectiveness, pre-exposure prophylaxis (PrEP) for HIV prevention remains vastly under-prescribed to women based on their need. Increasing PrEP uptake and persistence among women is crucial to reducing HIV transmission; however, there have been few studies designed specifically for women. This article describes the study protocol used to assess the feasibility, acceptability, and effectiveness of implementation strategies to improve PrEP uptake and persistence among Black women in the Midwest and South.

**Methods:**

PrEP Optimization among Women to Enhance Retention and Uptake (POWER Up) is an evidence-based, woman-focused set of five implementation science strategies that addresses barriers of PrEP utilization at the provider, patient, and clinic levels. POWER Up includes 1) routine PrEP education for patients, 2) standardized provider training, 3) electronic medical record (EMR) optimization, 4) PrEP navigation, and 5) PrEP clinical champions. These strategies will be adapted to specific clinics for implementation, tested via a stepped-wedge trial, and, if effective, packaged for further dissemination.

**Discussion:**

We will utilize a stepped-wedge cluster randomized trial (SW-CRT) to measure change in PrEP utilization across diverse geographic areas. Preparation for adapting and implementing the bundle of strategies is needed to determine how to tailor them to specific clinics. Implementation challenges will include adapting strategies with the available resources at each site, maintaining stakeholder involvement and staff buy-in, adjusting the study protocol and planned procedures as needed, and ensuring minimal crossover. Additionally, strengths and limitations of each strategy must be examined before, during, and after the adaptation and implementation processes. Finally, the implementation outcomes of the strategies must be evaluated to determine the real-world success of the strategies. This study is an important step toward addressing the inequity in PrEP service delivery and increasing PrEP utilization among Black women in the U.S.

## Background

### A focus on women and under-prescription of PrEP

Black/African American cisgender women (hereafter women) experience one of the highest HIV incidence rates among all subpopulations in the United States, second only to men who have sex with men (MSM). Despite constituting only 13% of the population, Black women account for 60% of new HIV infections among women in the U.S [1]. Moreover, Black women are disproportionately affected by HIV, with an 18-fold higher risk of acquiring HIV compared to white women [2].

In spite of a high HIV incidence, use of pre-exposure prophylaxis (PrEP) among Black women is very low. PrEP is highly effective for HIV prevention [3], but women make up a disproportionately low percentage of PrEP users compared to men. In 2021, the PrEP-to-need ratio (defined as number of PrEP prescriptions divided by number of new HIV diagnoses) for women was substantially lower than that for men (4.1 vs 11.2), indicating an inequity in PrEP use among women with respect to their need [4]. Black women in particular are underrepresented among PrEP users [5, 6]. Furthermore, among individuals who initiate PrEP, both women and Black patients are less likely to persist on PrEP compared to their white male counterparts [7, 8].

In addition to racial disparities in HIV incidence and PrEP use among women, prominent geographic disparities also exist. The South represents the greatest burden of HIV in the U.S. and ranks lower than other regions in terms of HIV prevention implementation. The majority of women who acquire HIV in the U.S. live in the South [2]. Although the region has more than half of new annual HIV cases, Southerners accounted for only 39% of all PrEP users in 2021 [9]. Additionally, women in the Midwest (4.57) and South (4.87) had the lowest PrEP-to-need ratios (indicating the highest unmet need for PrEP) among any subgroup in the U.S in 2021 [9]. Improving access to effective HIV prevention strategies for Black women in the Southern U.S. is critical to address these racial and geographic disparities and to eliminate HIV transmission in the United States.

### Addressing the barriers to PrEP initiation and persistence among women

There are several individual-, provider-, and clinic-level challenges to PrEP initiation and persistence for Black women [10]. PrEP awareness is limited in the community [11, 12], and Black women often have low self-perceived risk for HIV acquisition despite having certain risk factors; moreover, these risk factors among women were generally overlooked by previous guidelines for prescribing PrEP [13–15]. The Centers for Disease Control and Prevention (CDC) revised their PrEP guidelines in December 2021 to recommend that healthcare providers give information about PrEP to all sexually active adults and adolescents and to recommend PrEP for all adults and adolescents with risks for HIV exposure [16]. However, a significant proportion of medical providers do not routinely discuss PrEP or prescribe PrEP for their female patients [17, 18]. Indeed, most Black women would prefer to receive PrEP from trusted primary care providers [11], and the majority of women newly diagnosed with HIV attended medical visits prior to their HIV diagnosis, representing missed opportunities by medical providers for initiating PrEP [19]. Additionally, structural and social barriers exist to both PrEP initiation and persistence, including cost, healthcare access, stigma, lack of PrEP awareness/familiarity among patients, and comorbid substance use or mental health disorders [20–22]. Although there has been growing knowledge of ways to increase PrEP use by MSM and transgender women [23–27], much less is known about successful strategies to increase PrEP uptake and support PrEP persistence among Black women.

### Implementation of POWER Up

To improve PrEP uptake and persistence among Black women, multifaceted and multi-level strategies must target each step of the PrEP care continuum (i.e., awareness of PrEP, identification of PrEP-eligible candidates, prescription and initiation of PrEP, persistence of care during HIV risk periods, and re-initiation of care following discontinuance) [10]. Through preliminary work, our team has identified successful strategies for improving PrEP care continuum outcomes among Black women. We performed formative research guided by the Consolidated Framework for Implementation Research (CFIR 2.0) [28], including mixed methods studies of client-, health system-, and provider-level barriers and facilitators to PrEP initiation and persistence among Black women [11, 29–33]. Through this work, we have identified a set of five strategies that have been successful in community health clinic (CHC) settings for PrEP Optimization among Women to Enhance Retention and Uptake (POWER Up). POWER Up strategies include 1) routine PrEP education to raise awareness of PrEP among Black women; 2) standardized provider training for how to identify women who are PrEP candidates, discuss HIV risk and teach women about PrEP, and prescribe PrEP and engage them in PrEP care; 3) electronic medical record (EMR) tools for identifying women who would benefit from PrEP, prescribing PrEP, and tracking PrEP outcomes; 4) PrEP navigation to assist with PrEP initiation and persistence; and 5) clinical champions for supporting the successful creation and implementation of PrEP-related processes (Fig 1). With these POWER Up strategies, a CHC in the Midwest has more than doubled the rate of PrEP uptake among Black women and maintained PrEP persistence rates above the national average (mean persistence among ciswomen of 8.1 months vs. 5.8 months nationally) [7, 29]. Our study will implement this bundle of strategies in 3 CHC networks (1 in the Midwest and 2 in the South), with the goal of increasing PrEP uptake and persistence among Black women.

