
#### Data collection: Implementation phase

In preparation for the implementation phase, we created a table of desired EMR variables that will be collected from each CHC throughout the implementation period (Table 1). These variables will be collected from July 1, 2023 to December 31, 2025. We discussed data specifications (e.g., demographic characteristics, PrEP prescriptions, sexually transmitted infections (STI) diagnoses, etc.) with site leaders and adapted the list of requested variables based on availability of elements within the EMR, the type of EMR used, and workflow of each CHC.

**Table 1 pone.0285858.t001:** Electronic medical record (EMR) data collected monthly during the stepped-wedge cluster randomized trial (SW-CRT).

*Primary Outcome*		
**Data Variable**	**Brief Description**	**RE-AIM Dimension**
PrEP uptake	Number of patients initiating PrEP	Effectiveness
*Secondary Outcomes*		
**Data Variable**	**Brief Description**	**RE-AIM Dimension**
Total patients eligible to learn more about PrEP	All patients eligible to learn more about PrEP according to study criteria. All patients 18 years or older, who are not HIV positive who have a medical encounter during which PrEP could be prescribed.	Reach
Demographics/clinical factors of total patients eligible to learn more about PrEP	Demographic data for patients eligible to learn more about PrEP.^a^	Reach
HIV risk assessment	Proportion of patients who undergo HIV risk assessment at each site	Reach
Demographics/clinical factors of patients receiving HIV risk assessment	Demographic data for patients who undergo HIV risk assessment.^a^	Reach
PrEP eligibility	Proportion of patients identified as PrEP eligible at each site.	Reach
Demographics/clinical factors of PrEP eligible patients	Demographic data for patients identified as PrEP eligible.^a^	Reach
Number of providers who educate patients about PrEP	Number of providers who offer PrEP education	Reach
Number of providers who prescribe PrEP	Number of providers who prescribe PrEP to participants	Reach
PrEP education	Proportion of patients who received PrEP education.	Reach
Demographics/clinical factors of PrEP educated patients	Demographic of patients who received PrEP education.^a^	Reach
PrEP offered	Proportion of patients offered PrEP.	Reach
Demographics/clinical factors of patients offered PrEP	Demographics of patients offered PrEP.^a^	Reach
PrEP navigation	Number of patients receiving PrEP navigation services	Reach

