We will collect both patient-level and clinic-level data from each CHC on a monthly basis. These data will be collected in two ways: 1) by the aggregation of data from patient-level EMR records and 2) by surveys among patients and providers designed to measure knowledge, beliefs, and satisfaction regarding PrEP and the implementation strategies. All EMR data will be collected during each of the three phases of the stepped-wedge trial: 1) pre-implementation; 2) transition, and 3) implementation phases. Table 1 shows the list of EMR variables that will be collected from each site on a monthly basis during the stepped-wedge trial. To obtain these EMR variables, we will aggregate data from individual patient records (~3,000) that meet each variable definition. No recruitment of patients is required for the monthly EMR data collection, as POWER Up is considered part of routine care. The survey data that will be collected vary in the stages of the stepped-wedge trial and the frequency of assessment. Some of these measures will be collected and evaluated monthly, and some will be collected once for pre- and post-implementation (i.e., pre-implementation and at the end of the implementation period). Clinical champions at each site will assist with monitoring adherence to implementation protocols at each site. Table 2 shows outcomes that will be collected via quantitative surveys and qualitative interviews based on the RE-AIM framework [37] and their associated time periods of collection. These surveys and interview guides will be composed of previously validated questions whenever possible and include CFIR domains to assess implementation success. CHC providers and patients will be recruited to complete these quantitative surveys and qualitative interviews via the same recruitment methods used for pre-implementation focus groups (e.g., provider recruitment emails and routine phone calls/recruitment flyers for patients).

**Table 2 pone.0285858.t002:** Data collected for evaluation of implementation using the RE-AIM framework.

Data Variable	Time Collected from Healthcare Network	Brief Description & Source of Data	RE-AIM Dimension
Change in provider knowledge and attitudes about PrEP	Once during control period (baseline) and once at end of implementation period	Average change in score between baseline and post implementation survey about provider knowledge and attitudes about PrEP; qualitative interview	Effectiveness

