#### Quantitative data

For EMR variables, we will use descriptive statistics to examine the distribution of the data. We will compare the distribution of patient characteristics between the unexposed observations from the control period and the exposed observations during the implementation period. Outcome rates will be plotted over each six-month time period, comparing how rates differ from the control period to the implementation period between CHCs within a geographic area (Midwest or South), as well as within each CHC, to examine the effects of the implementation site and calendar time on outcomes. Additionally, rates will be compared by geographic area to detect differences in implementation effect size between the Midwestern and the Southern sites. We will use an intention-to-treat analysis to ensure that if a CHC deviates from the assigned implementation timeline (i.e., they begin the implementation of the bundle of POWER Up strategies earlier or later than planned), the most conservative estimate of the size of the implementation is used. To examine treatment effects for the effectiveness and individual maintenance outcome related to PrEP uptake (initial prescriptions and refills), we will use a generalized linear mixed model, with a random effect for each CHC and a random effect of time per CHC [35, 43–45].

For RE-AIM outcomes, we will first use descriptive statistics to examine the distribution of the data. Bivariate analysis will be employed to explore differences between groups (e.g., differences between clinics or time points). Fisher’s exact test and chi-square tests (for categorical variables) and t-tests (for continuous variables) will be used to identify factors correlated with RE-AIM outcomes. All statistical analyses will use two-tail alpha to reject null hypotheses at 0.05. To measure associations of various factors with RE-AIM outcomes, we will report odds ratios along with 95% confidence intervals. Statistical assumptions such as data normality will be confirmed, or data transformations or alternate non-parametric methods that do not break model assumptions will be used. We anticipate nominal missing data, but we are willing to consider methods such as multiple imputation if needed to preserve sample size.

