## Discussion

To effectively scale up our implementation strategies for use in CHCs, we need to monitor and evaluate each adaptation and modification step. Monitoring adaptation will ensure our strategies continue to support the overall model for our desired outcome of increased PrEP uptake and persistence among all patient populations, especially Black women. Successful implementation will begin with training of clinical staff followed by preliminary and setting-specific modifications, then adoption and evaluation of multilevel outcomes. As part of this project, we will complete multiple steps of iterative modification, implementation, and evaluation of our strategies to refine and test the POWER Up strategies for wide-scale use in CHCs in the Midwest and South. Our team will help facilitate provider training sessions, disseminate patient education materials, provide technical and logistical support for EMR updates, and serve as a resource for PrEP navigators and clinical champions. We will continually monitor the implementation process at each site to further adapt and support as needed. Lastly, we will measure the acceptability and fidelity of each strategy to gain additional feedback on the strengths and weaknesses of the strategy bundle and determine via EMR data if we achieved our goal (increased PrEP uptake).

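### Several secondary Reach items are read from the same EMR that the bundle modifies, so a control-to-implementation change in them may partly reflect better recording

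*Protocol article*

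**What the plan says.** **The EMR change is part of the treatment.** The abstract's Methods lists "electronic medical record (EMR) optimization" among the five strategies. Implementation of POWER Up describes it as "electronic medical record (EMR) tools for identifying women who would benefit from PrEP, prescribing PrEP, and tracking PrEP outcomes". In the Discussion, the team says it will "provide technical and logistical support for EMR updates". Settings states that no participating site has run the bundle before.

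**The EMR is also the measuring instrument.** Every Reach row stands in Table 1, the EMR table. Examples are "Proportion of patients who undergo HIV risk assessment at each site" and "Proportion of patients identified as PrEP eligible at each site"; education, offer and navigation follow the same pattern. Values are built by aggregating individual records (about 3,000) that satisfy each variable's definition. The timing is explicit: "All EMR data will be collected during each of the three phases of the stepped-wedge trial". Table 2, which covers surveys and interviews, has no Reach row.

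**The conditions are compared.** Study design says that change from control to implementation will be assessed for clinical and implementation outcomes. The Quantitative data section plots EMR outcome rates by six-month period, "comparing how rates differ from the control period to the implementation period". It also allows bivariate tests of RE-AIM outcomes between clinics or time points, at a two-sided 0.05 level. The mixed model is assigned to the outcomes based on prescriptions and refills.

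**The concern.** A count of records that meet a definition depends on two things: how often the step happens, and how often it leaves a countable entry. Strategy 3 is meant to act on the first and may well act on the second, because it supplies tools to identify candidates and track what follows. Provider training on the same steps could add to this.

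For items that exist only when staff document them, a rise between conditions could therefore be better care, better recording, or both. Randomising the order of roll-out does not separate them, because recording would change with condition at each clinic. Setting aside the six-month transition period does not help either, since any recording difference would last through implementation.

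What is at stake is the reading of the care continuum. Aim 3 produces an implementation guide from these results. If recording improved more at one step than at another, adopters could be told that the wrong step had responded.

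**Working it through.** The document states no Reach calculation, so there is no figure to reproduce. The check has three parts.

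**1. Which items are exposed**

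| Table 1 item | What creates the record | Exposure |
|---|---|---|
| HIV risk assessment, education, offer, navigation, number of providers who educate | Staff documentation of the step | Exposed |
| PrEP eligibility identified | Identification, which is what the EMR tool is for | Exposed |
| Total patients eligible to learn about PrEP | Age, HIV status, encounter | Much less |
| Number of providers who prescribe | Prescription data | Much less |
| PrEP uptake (primary), both persistence measures | Prescription data | Much less |

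**2. Size under assumed capture rates**

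Let p be the true proportion reached, the same in both conditions, and let s0 and s1 be the probabilities that a step is recorded in control and implementation. Assume no false records. Then:

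- recorded rate = p × s
- recorded ratio, implementation to control = s1 / s0 when p is unchanged
- odds ratio = [p·s1 / (1 − p·s1)] / [p·s0 / (1 − p·s0)]

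None of p, s0 and s1 is in the document. Taking p = 0.20 and s1 = 0.90, the implementation rate is 0.20 × 0.90 = 0.18.

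| s0 | Control rate | Implementation rate | Odds ratio |
|---|---|---|---|
| 0.25 | 0.20 × 0.25 = 0.05 | 0.18 | (0.18/0.82)/(0.05/0.95) = 4.17 |
| 0.75 | 0.20 × 0.75 = 0.15 | 0.18 | (0.18/0.82)/(0.15/0.85) = 1.24 |
| 0.90 | 0.20 × 0.90 = 0.18 | 0.18 | 1.00 |

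With p = 0.50 and s1 = 0.90, control capture of 0.80, 0.50 and 0.20 gives 40%, 25% and 10% against 45%. The odds ratios are 1.23, 2.45 and 7.36. Equal capture again gives 1.00.

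**3. Whether existing text closes the gap**

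- Data collection: Implementation phase says the requested variables were adapted to the elements available in the EMR, the EMR type and each clinic's workflow. That is a partial safeguard. It does not require a field to be filled equally before and after the EMR change.
- The monitoring board reviews data accuracy and completeness in general terms. No check against a source outside the EMR is described.
- The surveys cover knowledge, beliefs and satisfaction, not receipt of an assessment, education or an offer.

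**The case against.** The strongest objection is that poorer recording in control is inferred. The document does not say that the Table 1 fields are created by the new tools, or that they are empty or under-used beforehand. The variable list was fitted to what the EMRs held, and Trial status places the trial in its control period at the time of writing. This stands in part. The bias is conditional, its size is unknown, and zero is within the range. It does not remove the point, because an available field need not be used equally in both conditions.

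The second objection is that Reach is secondary. The mixed model covers prescription outcomes, the phrase about comparing control with implementation describes plots, and the tests on RE-AIM outcomes are exploratory. This also stands, and it limits the weight of the point.

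Three stronger readings are tempting, and the document supports none of them:

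- **The Reach results are biased.** The document shows only that the instrument is part of the intervention. Whether capture differs is not stated.
- **The primary result is compromised.** Uptake and persistence rest on prescriptions, which are much less dependent on new documentation tools.
- **The hypothesis of at least 50% reach is undermined.** It is an absolute target with no control contrast, so differential capture between phases does not affect it. Incomplete recording in implementation would make it harder to meet: at 90% capture, true reach of 0.50/0.90 = 55.6% is needed to record 50%.

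Finally, dropping every control contrast on Reach would discard usable baseline data at clinics whose fields already existed. That is right, and the fix below does not ask for it.

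**Conclusion.** The point holds in conditional form, as a modest improvement to the plan. The document states that the EMR tools belong to the bundle, that Reach is read from the EMR in all phases, and that the conditions are compared. Nothing in it ensures equal recording before and after the EMR change.

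If control capture is lower, the before/after change in risk assessment, eligibility identified, education, offer and navigation is at risk of bias in the bundle's favour. With true reach unchanged at 20% and 90% capture after go-live, the spurious odds ratio runs from 1.0 at equal capture, through 1.2 at 75% control capture, to 4.2 at 25%. All of these inputs are assumptions, and the document gives no basis for choosing among them.

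One related item needs the same care. The hypothesis that 10% of PrEP-eligible Black women will initiate PrEP uses an eligible denominator. If eligibility means identified by the tool, that denominator would change with condition in any cross-phase comparison.

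**What to change.** 1. In Table 1 or the data specification, flag each variable that comes from elements present and recorded the same way in each clinic's EMR before and after the bundle.
2. For any eligibility rate or eligible denominator compared across phases, define eligibility from those pre-existing elements (for example STI tests and diagnoses, encounters and demographics), and apply the definition identically in all periods.
3. Limit control-versus-implementation effect claims on Reach to the flagged variables.
4. Report the remaining items as *documented reach*: implementation-period levels against any target set for them, with control-period values shown descriptively and not read as an effect of the bundle.

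If the sponsor wants to keep a before/after contrast on an unflagged item, a sample could be checked in both conditions by chart review or patient report.

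The cost is a flag column and some analysis wording. No new clusters or redesign are needed. The downside is that some Reach items lose a formal before/after test at clinics whose fields are new. The optional validation sample would add data-collection work.
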